**Title**

| **Short Title** | 2 Young Lives (2YL) |
| --- | --- |
| **Aim** | To assess the feasibility and implementation of a mentoring programme for pregnant teenagers in Sierra Leone |
| **Sponsor** | Kings College London |
| **Funder** | NIHR Global Health Research Group |
| **Funding Reference Number** | NIHR133232 |
| **Duration (months)** | Funding period = 36 months, trial period = 24 months |
| **Grant activated** | 1 September 2021 |
| **Anticipated start date** | September 2021 |
| **Anticipated end date** | August 2024 |
| **Version Number and Date** | Version 2.1, 21 July 2023 |

# Background and rationale for study

Maternal mortality in Sierra Leone is one of the highest globally (1,360 deaths per 100,000 live births in 2015)^1^ with teenage pregnancy a leading cause of death for mothers; teenage mothers are 40-60% more likely to die during childbirth.^2^ However due to ineffective maternal death reporting, this could be significantly higher. A household survey conducted in 2015 indicated a maternal death rate of 1 in 10 for under-18-year-olds in Eastern Freetown. A following study examined the causes of this high incidence of maternal death in teenagers and highlighted intersecting health and socio-economic vulnerabilities.^3^ Among key findings were that pregnant teenagers are often neglected by their families, particularly when being cared for by a non-parental adult, often sleeping on bare ground without a mosquito net, and are fed once a day in exchange for heavy domestic duties such as water collection and laundering, in many cases with little protection from ongoing gender-based violence. This lack of adult care or support often leads to delays in care-seeking or complete lack of antenatal and delivery care, putting teenagers at high risk of death from undetected pre-eclampsia, untreated infections, anaemia, lack of birth preparation, and common obstetric risks.^3^ To achieve the Sustainable Development Goals target of reducing the maternal mortality rate to less than 70 per 100 000 live births by 2030, adolescent girls are a priority group. ^4-6^

These findings led to the development of 2 Young Lives (2YL), a locally-designed intervention that provides mentoring from pregnancy through to one-year post-birth for women aged under-18. This encourages mentees to take up antenatal care and hospital birth, re-establish family connections where this is safe and appropriate, promotes health-seeking behaviour, provides practical advice about childbirth, parenting and contraception, and supports mentees to return to education or start vocational training. The 2YL scheme was piloted in 2017/2018 in an urban suburb of the capital, Freetown, and expanded to new sites in 2018, 2019 and 2021.^7^

An initial evaluation of the 2YL intervention compared outcomes of young women pre-intervention (n=86) with those of other women post 2YL intervention (n= 67).^7^ In the 2YL cohort of young women who had mentors there were fewer maternal deaths (0% vs 10%) and lower levels of perinatal mortality (6% vs 16%), and infant mortality (11% vs 26%). Nearly all women receiving the 2YL intervention gave birth with a skilled birth attendant (SBA) and breastfed for longer than 6 months; and more than two thirds were using contraception by the baby’s first birthday, with no second pregnancies. In terms of fidelity of the intervention, mentors are required to provide at least one opportunity per week for a confidential 1:1 meeting, however most provided almost daily contact. All of the 2YL young women successfully ran a small business with support from their mentor, allowing them to learn business skills, eat well throughout pregnancy and provide for their baby. They reported increased self-confidence, supportive peer relationships, and a high level of satisfaction with the mentoring scheme. Subsequent anecdotal evidence is also now showing that the community engagement strategy pursued as an integral part of the early implementation is influencing more widely on ingrained attitudes towards practices which perpetuate gender inequality such as school non-attendance in pregnancy and child marriage.

Based on this preliminary data, the 2YL mentoring scheme is promising; it has potential to reduce maternal, neonatal and infant deaths rates, and sustainably improve livelihoods. However, a pilot trial is needed to assess the feasibility of recruitment, retention, collection of data and evaluation design. Such a trial and process evaluation should draw on the six core elements considered in the updated MRC framework for evaluating complex interventions which include: interacions between intervention and context, theoring how the intervention may work, diversity of stakeholders perspectives in research, uncertainainties, refinement of the intervention and resource and outcome consequences of the intervention.^8^

# How the 2YL intervention may work

Overall, the aim of 2YL is that mentees and their babies survive birth and the postnatal period, and that these young women are empowered economically and socially to thrive. A theory of change diagram in Figure 1 in page 8 illustrates how and why the 2YL intervention may work in young women in Sierra Leone.

After community engagement with key community stakeholders, volunteer mentors are recruited and trained to support mentees across a number of domains. The 4-day manualised training programme uses discussion, role play and bespoke pictorial maternal health resources to learn and share important health messages. Key ingredients of the mentoring scheme include a weekly one to one meeting, promotion of health services uptake, monthly social gatherings for peer support and health discussions, advocacy and practical advice, support to start and run small businesses, and encouragement to return to education or start vocational training.

There are a number of mechanisms whereby being mentored could lead to improved health outcomes for mothers and their babies:

- Mentors ensure that girls access antenatal care, often paying for routine drugs when not available in the clinics, and directly observing the girls taking them. They ensure birth with a Skilled Birth Attendant, a proven life-saving intervention. In addition, the timeliness and quality of this care, and the quality of interaction with the girl in the health facility may be improved by the her being accompanied by a known and respected older woman in the community^9^; mentors are often allowed to be present for birth. Getting to know a health worker through monthly facilitated discussions and regular antenatal care could also increase girls’ confidence in the health service, increasing their likelihood of seeking care in labour or in an emergency. Similarly, having a trustworthy adult in their lives also allows mentees to ask advice of mentors and access care promptly.
- Girls are economically empowered through their small businesses, which could lead to a better diet in pregnancy, potentially addressing risk factors for maternal mortality such as malnutrition and anaemia. This economic empowerment could also allow girls to make independent decisions when to go to hospital as they could pay for their own transport^10^.
- After birth, mentors promote basic health and healthy parenting practices, such as uptake of immunisations, making healthy local weaning food, talking and singing to babies, recognition and first line treatment of common childhood illnesses and early health-seeking behaviour. This knowledge and support could promote behaviours which reduce risk factors for infant death.

Mechanisms by which mentoring might lead to young women being empowered economically, socially and educationally:

- Mentoring increases self-confidence, a sense of agency and the ability to make changes which allow mentees to make decisions and pursue personal goals. Having a trustworthy adult and peers going through a similar experience in their lives promotes better mental health, and encourages returning to education or training which leads to financial and social benefits to herself, this child and future children. In addition, educational empowerment about their human and health care rights could equip both mentors and mentees to report and escape gender-based violence, and advocate for themselves and each other at health facilities to receive more respectful and timely care. For girls whose babies die, the loving care given by the mentor can promote resilience and supports emotional wellbeing.
- Stakeholder engagement with teachers (October 2021) has led to an additional element to the intervention; the training of teachers to be school teenage pregnancy champions to action a new government policy aimed at reintegrating adolescent mothers back into school (the radical inclusion policy). The theory of change for this addition is that as schools become more aware of the rights and needs of pregnant girls and young mothers, this will make schools more enjoyable places to be, and girls will be more likely to stay in school with all its short- and long-term benefits for wellbeing.
- Educational bursaries: though not an intrinsic part of the intervention, 15 girls were given bursaries in September 2021 to return to school (with a small grant through KCL). During stakeholder engagement, it became clear how highly valued this was in terms of empowerment and wellbeing, with proposed mechanisms being their acceptance by family, and their sense of purpose and achievement. Additional partner funding will be sought to add this element to the trial intervention.

In addition, at a community level, respectful community engagement and involvement in the establishment of the scheme, including wider discussions about teenage pregnancy and child marriage can lead to wider socio-cultural changes to attitudes and practices. There is also some evidence of health workers being held to account when making demands for payment for maternity services.

[figure not shown]

# Study aim

The overall aim of this pilot trial is to assess the feasibility and implementation of the 2YL mentorship scheme for young pregnant women in Sierra Leone to inform trial procedures for a subsequent fully powered cluster RCT evaluating the clinical, social and economic impact of the 2YL. This study will allow us to assess acceptability and feasibility of recruitment, retention, data collection, analysis and potential treatment effects, while also determining factors to optimize the intervention.

# Study objectives

Primary objective

To determine whether a pilot trial of the 2YL mentorship scheme for pregnant teenagers is feasible and to inform a future larger trial to evaluate the effectiveness of 2YL in improving pregnancy outcomes for mothers and babies in Sierra Leone.

Secondary objectives

To assess the integrity of study protocol including: recruitment, randomization procedure, data collection, retention and follow-up procedures, acceptability of intervention, primary outcome measure and sample size calculation, refinement of the intervention and training and supervision procedures, and estimation of resource use and costs.

To assess health, social, educational and economic outcomes of the 2YL intervention for young mothers and babies

To explore experiences, mentoring and thriving among young women receiving the 2YL intervention compared to those receiving usual care.

To evaluate the implementation, context and mechanisms of change of the 2YL intervention in order to understand the results and its potential impact.

# Methods

# Study design, setting and population

The design is a pilot cluster randomised controlled trial (cRCT) of the introduction of the 2YL mentoring adjunct to maternity care in Sierra Leone. The RCT will run in the communities served by the following 12 areas, representing a range of urban and rural settings:

| 1. Tombo town CHC | 7. Moriba Town (Lower Banta) CHP |
| --- | --- |
| 2. Mattru Town CHC | 8. Madina (Bum) CHC |
| 3. PAYCY's Clinic | 9. Senehun (Kamajei) CHC |
| 4. Taiama (Kori) CHC | 10. Moyamba Junction CHC |
| 5. Lengekoro CHP | 11. Heremakono MCHP |
| 6. Calaba Town CHC | 12. Yataia CHP |

The Standard Protocol Items Recommendations for Interventional Trials (SPIRIT) Figure adapted for the 2YL trial is shown below in Figure 1:

|  |  | **STUDY PERIOD** | | | | | | | | | | |  |  |
| --- | --- | --- | --- | --- | --- | --- | --- | --- | --- | --- | --- | --- | --- | --- |
|  | **Randomi-sation** | **Post-allocation** | | | | | | | | | | |  | **Close out** |
| **Timepoint*** | ***t_0_*** | ***t_1_*** | ***t_2_*** | ***t_3_*** | ***t_4_*** | ***t_5_*** | ***t_6_*** | ***t_7_*** | ***t_8_*** | ***t_9_*** | ***t_10_*** | ***t_11_*** | ***t_12_*** |  |
| Allocation | X |  |  |  |  |  |  |  |  |  |  |  |  |  |
| **Intervention** |  |  |  |  |  |  |  |  |  |  |  |  |  |  |
| *[2YLs+ usual care]* |  |  |  |  |  |  |  |  |  |  |  |  |  |  |
| *[Usual Care]* |  |  |  |  |  |  |  |  |  |  |  |  |  |  |
| **Assess-ments:** |  |  |  |  |  |  |  |  |  |  |  |  |  |  |
| *Composite primary outcome* |  | X | X | X | X | X | X | X | X | X | X | X | X |  |
| *Secondary outcomes* |  | X | X | X | X | X | X | X | X | X | X | X | X |  |

****_0_***, ***t_1-12_*** = Two months-time period

Figure 1. SPIRIT figure adapted for the 2YL trial

Sierra Leone is classified as a low-income country and has one of the highest mortality rates in the word, with a high burden of communicable and non-communicable diseases. It struggles to provide basic universal health coverage (UHC) and potable water and sanitation. Sexual violence and rape are common, and capacity to provide treatment to affected women and girls is extremely limited (State of Emergency over rape and sexual violence was declared in 2019). Sierra Leone also suffers an inadequacy of human resources for health; it has 2 skilled providers (doctors, nurses and midwives) per 10,000 population which is well below WHO’s health workforce targets for UHC and Sustainable Development Goal of 23.

Suboptimal maternal health care contributes to premature deaths, disability, and devastating spending in a country with an incipient financial crisis exacerbated by the 2014 Ebola epidemic (and further weakened during the ongoing COVID-19 epidemic). It has the highest maternal mortality rates in the world (1,360/100,000) with teens accounting for nearly 40% of all maternal deaths (more than two thirds caused by pre- eclampsia, haemorrhage and sepsis). Neonatal, infant and child mortality are also high (31.8, 83.5 and 11/1,000 respectively) and infants of mothers who die are up to 10 times more likely to die within their first 2 years. Antenatal attendance, access to skilled birth attendants and facility deliveries are low, and quality service delivery is often poor with disparities in access and availability to appropriate assessment and intervention, with delays in delivery, escalation of care and emergency maternity care.

Participants

Inclusion criteria

- Pregnant women aged under 18 at recruitment

Exclusion criteria

- There will be no exclusion criteria in terms of gestational age, as from an ethical and logistical standpoint, all young pregnant women should have access to the intervention, and pregnancy outcome data to be collected at an individual level.

Clusters and participant selection and enrolment

A flow chart for 2YL is presented in Figure 2. Twelve PHUs have been identified by local partners, and matched into pairs with corresponding delivery rates and distance to a referral hospital (Appendix 1). From these pairs, PHUs will be randomly allocated into intervention sites and control sites. With established approval from the Ministry of Health and Sanitation, health leaders at a district level will be approached by local research staff with an invitation for their PHUs to participate in the study. On the basis of local baseline data, we estimate that 36 women per PHU will participate, approximately 216 women per arm (Figure 1) (details of sample size calculations in page 23). In the event of changes to the PHUs serving a community during the study period (e.g. existing PHUs closing, new PHUs opening), we may invite a PHU to participate in the same randomised arm if it is serving the same community . Our rational is that this is a trial of a community-based intervention, we have allocated a treatment arm to the community, and the community are now accessing another facility. This approach will help us to maintain recruitment to both arms. For example, Yataya community has been randomised to the control arm. The new PHU that recently opened there will be automatically allocated to the control arm. We may also conduct a community based survey in those clusters with low numbers of pregnant adolescent girls to understand if numbers included in the trial are real or if there is overreporting of age in facilities.

In intervention sites, an established process of three community engagement visits will ensure buy-in of the intervention from key stakeholders and community members, and allow volunteer mentors to be recruited. Mentors are women selected based on being well known and respected in communities, having a reputation for kindness and being trustworthy, and having an existing interest in young women’s issues. This is followed by a 4-day manualised training course delivered by an experienced educationalist and in-country co-ordinator. Pregnant girls often self-refer or are brought by a friend or family member who has heard about the mentoring scheme from the community engagement activities. As per normal 2YL practice, the local team co-ordinator will meet with eligible pregnant girls and enrol them in the mentoring scheme as they come forward to a maximun of 36 per month (maximum number of girls that mentors can support per cluster due to limited resources). This help us to test the feasibility of the intervention in a pragmatic way while avoiding selection bias. An information leaflet will also be provided to girls in intervention clusters before enrolling in the mentoring scheme to help them understand the research, and what it involves to enable them to make an informed choice. Verbal consent will be obtained and recorded in the mentors’ registry book.

k=12

Randomisation

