**Recruitment, consent, data collection** ≈**3-6 and** ≈**9-12 months**

Interviews, focus groups, photovoice

**(Routine data collection at 1year** (routine PHU visit)

**(Routine data collection at 1year** (routine PHU visit)

Figure 2. Two Young Lives pilot study flowchart

Randomisation

The unit of randomisation is the trial area (or cluster), rather than individual woman. The sixteen trial areas will be allocated cluster numbers. Randomisation will be managed via a secure web-based randomisation and data management system hosted by MedSciNet with telephone back-up available at all times. Randomisation to intervention sites (2YL) and control sites (usual care) will occur in a 1:1 ratio. A minimisation algorithm will be used to ensure balance between the groups with respect to PHU use and distance to referral hospital. MedSciNet will write the randomisation program and hold the allocation code.

Intervention: 2YL mentoring scheme + usual maternity care

Women in the intervention group will receive the 2YL mentoring scheme provided as an adjunct to usual maternity care. Using the TIDieR reporting guidance^11^, a description of the intervention is as follows:

*Brief name*. 2 Young Lives mentoring scheme for pregnant teenagers and young mothers in Sierra Leone.

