*What? (Procedures) and How? (Modes of delivery)*. Weekly meetings between mentor and mentee; going to a local health facility with mentee to register for antenatal care, and reminding to attend or attending with mentee for usual antenatal care; accompanying mentee to health facility when in labour or needing emergency care (or ensuring other birth partner is available according to mentee’s wishes); flexible support postnatally dependent on mentee’s support network; discussion with mentee to consider small business options and accompanying mentee to purchase first supply of goods; monthly site meetings with all mentors and mentees for social interaction, cooking, eating and group discussion using Welbodi health cards; visits from mentor to mentee’s family to advocate for family support, if safe and appropriate; a face-to-face training for teachers in each of the 8 intervention sites. Graduation celebration at the end of the mentoring scheme.

*Who provided?* Mentors and teachers are trained by an experienced educationalist with experience of training both cadres. Mentors are women selected from communities where mentoring will take place, recruited based on having a reputation for kindness and being trustworthy, and an existing interest in young women’s issues. Visitors at monthly meetings are HCPs from local health facilities, or other or other community members who talk about educational or training opportunities.

*Where?* Mentoring takes place in agreed venues in the community where the mentee feels comfortable and where mentee and mentor can have a confidential conversation. Monthly meetings take place in a location in the community where there is shaded space for a group of 15-20 to cook (outdoors on a fire) and eat; many villages have these shared spaces, or mentors’ compounds where there is tree-shade.

*When and how much?* Girls are recruited at any stage of pregnancy, and have at least weekly mentoring as described, until baby is one year old.

*Tailoring?* If mentees are identified who have physical or intellectual disabilities, the programme is tailored to their needs where possible. For example, by providing communication cards for a deaf girl to use in labour, or by monitoring a girl with a learning disability taking pregnancy medication.

*Modifications? 10. How well planned? 11. How well actual?* These elements will be reported on at points in the research cycle when formative evaluation of implementation is undertaken.

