# Appendix 1: 2YLs prospective sites

| **Town/ village** | **Chiefdom** | **District** | **Name of PHU** | **Number of SVD births in 2020** | **2020-Total number of biths (SVD, assisted, CS), all ages** | **2020-Total number of biths (SVD, assisted, CS), <19** | **Rate** | **Nearest hospital for CS** | **Distance/**  **time taken to travel to hospital** | **Site number for randomisation** |
| --- | --- | --- | --- | --- | --- | --- | --- | --- | --- | --- |
| Moriba Town | Lower Banta Chiefdom | Moyamba | Moriba Town (Lower Banta) CHP | 147 | 135 | 55  (4-6 p/month) | 33% | Moyamba Government Hospital | 71km,  1hr 53 min | 1b |
| Mattru Town CHC | Jong chiefdom | Bonthe | Mattru Town CHC | 67 | 60 | 28  (2-3 p/month) | 64% | Bo Government Hospital | 81km,  2hrs, 3 min | 2a |
| Madina | Bum chiefdom | Bonthe | Madina (Bum) CHC | 121 | 100 | 39  (3-6 p/month) | 46% | Bo Government Hospital | 125km,  2hrs, 47 min | 2b |
| Senehun | Kamajei chiefdom | Moyamba | Senehun (Kamajei) CHC | 95 | 77 | 30  (2-6 p/month) | 60% | Bo Government Hospital | 38km,  31 min | 3b |
| Taiama | Kori Chiefdom | Moyamba | Taiama (Kori) CHC | 102 | 99 | 38  (2-5 p/month) | 47% | Bo Government Hospital | 51km,  43 minutes | 4a |
| Moyamba Junction | Fakunya chiefdom | Moyamba | Moyamba Junction CHC | 115 | 102 | 45  (3-6 p/month) | 40% | Moyamba Government Hospital | 34km,  31 minutes | 4b |
| Lengekoro | Diang chiefdom | Koinadugu | Lengekoro CHP | 112 | 97 | 41  (3-5 p/month) | 44% | Kabala Government Hospital | 22 km,  22 minutes | 5a |
| Heremakono | Wara wara yagala chiefdom | Koinadugu | Heremakono MCHP | 118 | 123 | 56  (4-6 p/month) | 32% | Kabala Government Hospital | 12 km,  14 minutes | 5b |
| Yataya | Wara wara yagala chiefdom | Koinadugu | Yataya CHP | 90 | 78 | 28  (2-4 p/month) | 64% | Kabala Government Hospital | 6km, 14 minutes | 6b |
| Tombo | York rural zone | Western Rural | Tombo town (York rural) CHC | 119 | 100 | 49  (variable, some months >10 others <4 or none?) | 37% | PCMH | 42 km,  1hr, 3 minutes | 7a |
| Kaningo | West 3 Zone | Western Urban | PAYCY's Clinic | 147 | 157 | 65  (6-10 per month) | 28% | PCMH | 5km,  20 minutes | 8a |
| Calaba Town | East 3 | Western Urban | Calaba Town CHC | 90 | 79 | 30  (3-5 per month) | 60% | PCMH | 3km,  12 minutes | 8b |
|  |  |  |  |  |  |  | 45.5% |  |  |  |

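### The protocol gives two incompatible allocation schemes and two cluster counts, and the appendix cited for the matched pairs does not show them

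*Protocol*

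**What the plan says.** **Number of areas.** Study design, setting and population: "The RCT will run in the communities served by the following 12 areas". The flow chart shows 12 clusters split six and six. The enrolment text expects 36 women per PHU and about 216 per arm, which is also six PHUs per arm (36 × 6 = 216). The Randomisation section says "The sixteen trial areas will be allocated cluster numbers". The intervention description (procedures) provides for "a face-to-face training for teachers in each of the 8 intervention sites".

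**Allocation scheme.** The enrolment text says "Twelve PHUs have been identified by local partners, and matched into pairs with corresponding delivery rates and distance to a referral hospital (Appendix 1"), followed by "From these pairs, PHUs will be randomly allocated into intervention sites and control sites". The Randomisation section does not mention pairs: "Randomisation to intervention sites (2YL) and control sites (usual care) will occur in a 1:1 ratio", and "A minimisation algorithm will be used to ensure balance between the groups with respect to PHU use and distance to referral hospital".

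**Appendix 1.** The column headed "Site number for randomisation" lists 1b, 2a, 2b, 3b, 4a, 4b, 5a, 5b, 6b, 7a, 8a and 8b.

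**Analysis and power.** Proposed analysis sets logistic regression with standard errors adjusted for clustering. It adjusts for important baseline differences and gives parity and gestation at first antenatal visit as examples. The sample size section states 84% power for 20% against 9%, with at least 42 deliveries per site and ICC 0.02. It states no number of sites, alpha or sidedness.

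**The concern.** Randomising within matched pairs and minimising across all areas are different procedures and call for different analyses. With so few clusters, the choice affects both the degrees of freedom and the precision. A reader cannot tell which was used, on how many areas, or which sites were paired.

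This is more than a drafting matter for a pilot. Randomisation is listed among the primary feasibility outcomes, and the randomisation procedure is an item in the secondary objective on protocol integrity. A procedure described in two ways cannot be assessed against its plan. The number of clusters also decides whether the stated power can be reproduced.

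**Working it through.** **1. Appendix 1 labels.** There are 12 sites over eight pair numbers.

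| Pair number | Labels listed | Complete? |
|---|---|---|
| 1 | 1b | no |
| 2 | 2a, 2b | yes |
| 3 | 3b | no |
| 4 | 4a, 4b | yes |
| 5 | 5a, 5b | yes |
| 6 | 6b | no |
| 7 | 7a | no |
| 8 | 8a, 8b | yes |

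Four numbers are complete and four have a single member. Twelve sites in pairs would need six complete pairs.

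**2. The stated 84%.** Inputs from the sample size section: m = 42, ICC = 0.02, p1 = 0.20, p2 = 0.09. Alpha is assumed to be 5%.

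- Design effect = 1 + (42 − 1) × 0.02 = 1.82.
- Effective n per arm = k × 42 / 1.82, which is 138.5 for k = 6 and 184.6 for k = 8.
- Power = Φ[(0.11 − z × √(2 × 0.145 × 0.855 / n)) / √((0.20 × 0.80 + 0.09 × 0.91) / n)].

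| Areas | Test | Calculation | Power |
|---|---|---|---|
| 16 (k = 8) | two-sided, z = 1.96 | (0.11 − 1.96 × 0.0366) / 0.0362 = 1.05 | 85.4% |
| 12 (k = 6) | two-sided, z = 1.96 | (0.11 − 1.96 × 0.0423) / 0.0418 = 0.65 | 74.1% |
| 12 (k = 6) | one-sided, z = 1.645 | (0.11 − 1.645 × 0.0423) / 0.0418 = 0.97 | 83.3% |

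So 84% fits roughly either 16 areas two-sided or 12 areas one-sided. The document does not say which.

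**3. What the scheme does to power with 12 clusters.** Effect / SE = 0.11 / 0.0418 = 2.63. Power comes from a noncentral t, two-sided 5%, on cluster-level summaries.

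| Analysis | df | Power |
|---|---|---|
| Unmatched | 10 | 66.1% |
| Unmatched, two cluster-level covariates, no precision gain | 8 | 63.7% |
| Six pairs, matching removes no variance | 5 | 56.3% |
| Six pairs, matching removes 20% of the variance of the pair difference | 5 | 65.6% |
| Six pairs, matching removes 50% | 5 | 84.1% |

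The variance reductions are assumptions that show the range; the protocol gives no figure for them.

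**4. Appendix 1 birth counts.** The 2020 count of SVD births exceeds the all-ages total (SVD, assisted and CS) at 10 of the 12 sites, for example 147 against 135 at Moriba Town. The exceptions are Heremakono (118 against 123) and PAYCY's Clinic (147 against 157). A volume covariate cannot be taken from this table unchecked.

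**The case against.** Several stronger readings are tempting, and the document does not support them.

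- **That four clusters were randomised without a partner.** Appendix 1 lists prospective sites, and numbers 1 to 8 with a and b suffixes would fit labels left over from a longer list of 16. The two-column site list in the design section reproduces pairs 2, 4 and 5 in its rows, so the other sites may have been re-paired. The columns are unlabelled, however, and on that reading PAYCY's Clinic (157 births, 5 km) would sit with Senehun (77 births, 38 km), whereas Appendix 1 codes it with Calaba Town. What is established is unpartnered labels, not unpartnered clusters.
- **That the analysis ignores the allocation factors.** The covariates are given as examples, and an analysis plan not shown here may add others. The protocol simply does not name the factors.
- **That the error rate is at risk.** Leaving out balancing factors or pairs usually makes standard errors too large, which is conservative.
- **That the scheme alone fixes the degrees of freedom, or that power is 56%.** A matched design can be analysed without its matching. The 56% is one end of a range, and the t-test is an approximation to the planned individual-level regression.
- **That the 84% was certainly computed for 16 areas.** The one-sided calculation with 12 areas fits about as well.

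It is also fair to say that feasibility is this pilot's primary objective, which limits the weight of any power argument. None of this removes the contradiction between the enrolment text, the Randomisation section, the intervention description and Appendix 1.

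**Conclusion.** The point stands as a contradiction within the current protocol: two allocation schemes, two cluster counts (12 with six per arm, against sixteen with 8 intervention sites), and an appendix from which the pairs used cannot be read.

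Its measurable consequence is for the power statement. Moving from 16 areas to 12 lowers two-sided power from 85% to 74% by the normal approximation, and to 66% with a cluster-level t-test on 10 df. These figures rest on the protocol's own rates, cluster size and ICC, and on an alpha of 5% that it does not state. For six pairs the figure could lie between 56% and about 84%, depending on how much variance matching removes. If the pairs or balancing factors were left out of the model, the expected harm is lost precision. Whether the analysis should be matched or unmatched cannot be decided from the labels; it depends on what was executed.

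**What to change.** Version 2.1 already reports that the Yataya community was randomised to control, so the procedure used should be on record.

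1. From the allocation record, state the one scheme executed for the 12 areas and delete the other.
2. Correct the references to sixteen areas and 8 intervention sites.
3. Relabel Appendix 1 with the pairs used, or remove the pair codes if there were none.
4. State the number of clusters, alpha and sidedness behind the power figure, and restate it for 12 clusters.
5. Prespecify that the primary model reflects the executed scheme: PHU birth volume and distance to referral hospital as cluster-level covariates if areas were minimised, or the pairs accounted for if areas were randomised within pairs.

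Items 1 to 4 cost wording and one recalculation. Under minimisation, item 5 costs about two degrees of freedom (10 to 8, or 66% to 64% power before any gain in precision). The Appendix 1 birth counts must be checked before they serve as a covariate. Because the enrolment text lets a PHU be added where the facilities serving a community change, the protocol should also say which facility's volume applies.
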